## Abstract

**Background:**

There are over 25 million people worldwide living with or beyond cancer and this number is increasing. Cancer survivors face a range of problems following primary treatment. One of the most frequently reported and distressing symptoms experienced by cancer survivors is fatigue. There is growing support for survivors who are experiencing problems after cancer treatment to engage in supported self-management. To date there is some evidence of effective interventions to manage fatigue in this population; however, to our knowledge there are no online resources that draw on this information to support self-management of fatigue. This paper describes the protocol for an exploratory randomized controlled trial of an online intervention to support self-management of cancer-related fatigue after primary cancer treatment.

**Methods/design:**

This is a parallel-group two-armed (1:1) exploratory randomized controlled trial including 125 cancer survivors experiencing fatigue (scoring ≥4 on a unidimensional 11-point numeric rating scale for fatigue intensity) within five years of primary treatment completion with curative intent. Participants will be recruited from 13 NHS Trusts across the UK and randomized to either the online intervention (RESTORE), or a leaflet comparator (Macmillan Cancer Backup, *Coping with Fatigue*). The primary outcome is a change in Perceived Self-Efficacy for Fatigue Self-Management (as measured by the Perceived Self-Efficacy for Fatigue Self-Management Instrument). Secondary outcomes include impact on perception and experience of fatigue (measured by the Brief Fatigue Inventory), and quality of life (measured by the Functional Assessment of Cancer Therapy - General and the Personal Wellbeing Index). Outcome measures will be collected at baseline, 6 weeks (completion of intervention), and 3 months. Process evaluation (including telephone interviews with recruiting staff and participants) will determine acceptability of the intervention and trial processes.

**Discussion:**

Data from this trial will be used to refine the intervention and contribute to the design of an effectiveness trial. This intervention will be expanded to address other cancer-related problems important to cancer survivors following primary cancer treatment.

**Trial registration:**

ISRCTN67521059

## Background

There are around 25 million people worldwide living with or beyond cancer [1], and this number is increasing. With improvements in early diagnosis and treatments, patients are also living longer after cancer and cancer is beginning to be viewed as a long-term condition [2]. It is, therefore, of growing importance that the needs of this population are identified and effective interventions developed to resolve or support management of cancer-related problems.

The amount of evidence of the range and prevalence of problems faced by cancer survivors after completion of treatment is increasing and we know that cancer-related fatigue (CRF) is a frequently reported and distressing symptom [3,4], which can persist for a number of years after completion of treatments [5,6]. The exact prevalence of fatigue is unknown and appears to vary by tumour type, treatments received and time since diagnosis. However, it is generally accepted that around one-third of people will experience fatigue within the first year following treatment [7,8], and some studies report significantly higher rates [9,10].

Despite the frequency and debilitating effect of CRF, the evidence for pharmacological treatment is sparse [11]. A meta-analysis [12] and Cochrane review [13] suggest that physical activity may improve fatigue; however, the type, duration and intensity of the exercise that might be of benefit are not yet known. There is also some support for the use of cognitive behavioural therapy [14] and psychosocial support [15]; however, there has been a call for the development of further non-pharmacological interventions to help patients manage this symptom [11].

The importance of people taking an active role in managing long-term health conditions is increasingly recognized. It has been reported that this can increase a person’s self-efficacy, which is in turn associated with improved quality of life [16]. There is also evidence that self-care behaviours improve physical and psychological symptoms [17]. Our own research indicates that a key component of self-management for cancer survivors involves the rebuilding of confidence after cancer treatment [18], and that this confidence is amenable to change [19]. An emphasis on supported self-management strategies is important from the perspective of health service planners and policy makers because of the ever-increasing number of patients living with long-term consequences of cancer and associated economic costs. Indeed, in England, the National Cancer Survivorship Initiative have highlighted supported self-management as one of their key areas for development, and the National Coalition for Cancer Survivorship (United States) and the Australian Cancer Survivorship Centre have been established to promote research and development of services for people living with and beyond cancer.

There is mounting evidence for the efficacy of online interventions in the management of physical symptoms such as pain [20]. Online interventions have the advantage of being widely available to those with internet access (83% of the population of Great Britain [21]) and have been found to be cost-effective [22]. With an increasing proportion of older adults having access to the internet, there has also been an emergence of online interventions for this population. A recent review by Aalbers *et al*. [23] concluded that complex online interventions in the over 50s, designed to promote health behaviour change, were effective.

The development of RESTORE, an online intervention designed to increase self-efficacy to manage CRF, followed the recommendations of the Medical Research Council framework for developing and evaluating complex interventions [24]. It was informed by the conceptual framework of self-management after cancer treatment previously described by Foster *et al*. [25] and is underpinned by the principles of self-efficacy theory [26]. Bandura proposes that there are four sources of self-efficacy: performance accomplishment, verbal persuasion, vicarious experiences and physiological states. The RESTORE online intervention therefore includes components designed to enhance self-efficacy through these sources. The development of RESTORE is described elsewhere [27].

This paper describes the protocol of the RESTORE exploratory randomized controlled trial (RCT) and is written following CONSORT guidelines [28] and informed by SPIRIT guidance [29] for clinical trials. The aim of this study is to test the value (proof of concept) of this intervention and determine whether its use increases self-efficacy to self-manage CRF following completion of primary cancer treatment.

## Methods

### Design

This is an exploratory, parallel-group RCT and has been registered with the International Standard Randomized Controlled Trial Number Register (ISRCTN67521059). Participants will be randomized in a 1:1 ratio to receive either the RESTORE online intervention, or a leaflet comparator developed by Macmillan Cancer Backup, *Coping with Fatigue*[30]. Participants are randomized in blocks of four, clustered by NHS Trust. An independent statistician wrote a program using the statistical software R to generate a sequence of numbers for each NHS Trust. It was not possible to blind the coordinating research team to group allocation and the nature of the trial is such that blinding to patients could not be achieved. Data analysts will be blinded to group allocation when examining differences between groups.

This study has received ethical approval from the NRES Committee South Central – Oxford A, and research governance approval from the University Hospital Southampton NHS Foundation Trust, REF RHM CAN0875. This study has also been adopted by the UK Cancer Research Network Portfolio (ID 12769), which provides network resources, including Research Nurse and Clinical Trial Officer support for recruitment.

### Setting and participants

Participants will be recruited from 13 NHS Trusts across the UK (including sites in England, Scotland, Wales and Northern Ireland). We aim to recruit 125 patients who have completed primary treatment with curative intent for non-metastatic cancer within the last 5 years. Recruitment will take place between September 2012 and June 2013.

Participants are eligible for the study if they (1) are over 18 years of age, (2) are experiencing fatigue defined as scoring ≥4 on a unidimensional 11-point numeric rate scale for fatigue as suggested by the National Comprehensive Cancer Network [31], (3) are able to complete written records in English, (4) have or are willing to create an email account and have access to the internet, (5) have completed primary treatment for invasive cancer (patients are eligible for the study if they are receiving monoclonal antibodies or endocrine treatment as maintenance therapy). Patients will be excluded if (1) in the opinion of a relevant clinician they are unable to give informed consent, (2) have a previously diagnosed mental health condition that is likely to be exacerbated by participation in the intervention, (3) are too ill to engage in the intervention (determined by a member of the patient’s direct clinical care team).

Patients will be referred by their direct care team at an end-of-treatment appointment or during follow-up clinics to the hospital research team (for example, research nurses and clinical trial officers), who will screen patients for inclusion in the study. Screening will involve a face-to-face discussion with a member of the team. The study will be explained and patient status documented. Possible outcomes are (1) eligible and willing to participate, (2) eligible and unwilling to participate, and (3) ineligible. Wherever possible, the reason for declining participation and ineligibility will be recorded.

Eligible and willing patients will be given a letter of invitation, patient information sheet, reply slip and Freepost envelope. Patients who, after reading the documentation, are happy to take part will be asked to complete the reply slip and return it to the coordinating research team at the University of Southampton. A member of the coordinating research team will then contact the patient and discuss the study, answering any questions. Patients will then be sent an email including the website address for the RESTORE intervention and a unique study ID number. Patients register with their email, chosen unique password and study ID number and complete the online consent form and baseline assessment. A member of the coordinating research team then determines group allocation from the randomized list and an email is sent to participants notifying them of their group allocation. See Figure 1 for patient flow through the trial.

**Figure 1 F1:**
[figure not shown]
Flow of patients through the trial.

### The intervention

The RESTORE online intervention was developed using LifeGuide, open source software [32].

The purpose of this intervention is to increase participant’s self-efficacy to manage CRF. Table 1 summarizes the intervention and the components’ association with self-efficacy theory. Briefly, patients have six weeks to complete the five sessions of RESTORE. Patients are presented with sessions one and two (which are compulsory) at weekly intervals and can then choose from sessions three to five for the following three weeks. For example, a participant may choose to visit the same session three times, or visit each session once. It is expected (based on development work) that each session will take approximately 30 minutes to complete, depending on the amount of time spent engaging in the suggested activities.

**Table 1 T1:** Intervention content and association with self-efficacy theory

**RESTORE sessions**	**Content**	**Mandatory/not mandatory**	**Self-efficacy theory construct**
Session 1: introduction	Defines CRF, possible causes and effects, and outlines purpose of the intervention	Mandatory	Not applicable
Session 2: goal setting	Introduces the concept of goal setting and planning; ‘SMART’ (specific, measurable, attainable, relevant, time-bound) goals are described	Mandatory	Performance accomplishments and verbal persuasion
Session 3: diet, sleep, exercise, home life and work	Describes how CRF may impact on these aspects of everyday life and how effective goal setting can help manage this interference	Not mandatory	Performance accomplishments and verbal persuasion
Session 4: thoughts and feelings	Psychological aspects of CRF and how these can be managed, including through goal setting	Not mandatory	Performance accomplishments and verbal persuasion
Session 5: talking to others	Describes the difficulties of talking to others (friends, family, colleagues, health professionals), and some strategies on how to manage this, including through goal setting	Not mandatory	Performance accomplishments and verbal persuasion
**Activities suggested throughout**			
Patient stories	Extracts from people affected by cancer and who have experienced fatigue; sharing their experiences and methods of self-management, written text and video clips	Not mandatory	Vicarious experiences
Self-monitoring	The use of a fatigue diary to monitor fatigue and understand its pattern	Not mandatory	Physiological experiences
	Monitoring fatigue each time a participant logs into RESTORE	Mandatory	
Feedback	Personal feedback on success of goal setting, planning and fatigue level	Mandatory	Performance accomplishments and verbal persuasion
Web links	Web links to useful resources	Not mandatory	Not applicable
Take a break buttons	Provided throughout to allow participants to rest during sessions if required	Not mandatory	Not applicable

The Macmillan Cancer Backup leaflet*, Coping with Fatigue* informed the content of the RESTORE sessions. Information and components of the intervention were also informed by the available evidence of fatigue management in cancer survivors. For example participants are encouraged to monitor activity patterns and engage in regular physical activity [12,13]. In addition, session four (managing thoughts and feelings) draws on the principles of cognitive behavioural therapy [14]. An expert design team supported the development of the RESTORE sessions.

Activities are available throughout RESTORE. These include a fatigue diary that can be downloaded from the website as a means of monitoring fatigue, in addition to completing a single-item assessment of fatigue during each session. Patient stories (as written text and video clips) are used throughout to provide examples of how people affected by CRF have managed the challenges faced. Automated tailored feedback based on goal-related progress and change in fatigue levels from the previous week are included throughout and there are links to useful resources such as mindfulness and relaxation training, and where to access information regarding financial support. ‘Take a break’ buttons are available during each session, allowing participants to rest if necessary.

During the trial, patients will receive automated emails encouraging them to complete the next session if they have not done so within seven days. Similar emails will be sent to prompt completion of outcomes measures.

### Comparator group

The leaflet *Coping with Fatigue* produced by Macmillan Cancer Backup will be sent to those in the comparator group. This information leaflet on managing CRF is widely available in the UK through local information services and used by clinical teams. Participants in the comparator group will be given access to the RESTORE online intervention once all outcomes measures have been completed.

### Assessments

During screening, the participant’s date of birth, sex and cancer type will be recorded to allow analysis of factors influencing uptake.

Baseline assessment (T0) will be completed online immediately after participants consent to the study and prior to randomization. Demographic information will include age, sex, ethnicity, marital status, educational status, accommodation type and postcode. Clinical information will also be abstracted from patients’ clinical records by a member of their hospital research team. This will include information on cancer diagnosis (date, type and stage) and treatments received.

The primary outcome measure is the Perceived Self-Efficacy for Fatigue Self-Management Instrument (PSEFSM) [33]. The instrument includes six items and respondents are asked to report their degree of self-efficacy in performing various tasks on an eleven-point scale. This measure has been shown to have good reliability (Cronbach’s coefficient αof 0.92), construct validity and generalizability [33].

A number of secondary outcome measures will be also assessed.

Self-efficacy for managing chronic disease will be measured by the Self-Efficacy for Managing Chronic Disease 6-item Scale [34]. This scale has response options from 1 to 10 (with 10 being most confident) for six items. Respondents are asked to rate their confidence in performing various activities. The scale has good internal validity and has been used in cancer populations [35].

Quality of life will be measured by the Functional Assessment of Cancer Therapy - General (FACT-G) [36]. This is a 27-item questionnaire consisting of four subscales: physical wellbeing (seven items), social wellbeing (seven items), emotional wellbeing (six items) and functional wellbeing (seven items). Respondents indicate how true each statement was for them during the previous seven days on a five-point Likert scale. Higher scores indicate higher quality of life. This measure has proven validity and reliability [36]. The Personal Wellbeing Index (PWI) will also be used to measure quality of life. This index includes seven items, which deconstruct the global question, ‘How satisfied are you with your life as a whole?’ and has been found to have good reliability (Cronbach’s α 0.70 to 0.85) [37]. Response options are 0 to 10, with higher scores denoting higher satisfaction with life.

Depression will be assessed using the Patient Health Questionnaire (PHQ-9). This is a nine-item scale consisting of two components; one assesses symptoms and functional impairment, the other assesses severity. This tool is based on the diagnostic criteria for depressive disorder. This is a reliable and valid measure of depression [38] and has been used extensively, including among cancer populations [39].

Fatigue will be assessed using the Brief Fatigue Inventory. This is a nine-item scale. Items one to three assess current, usual and worst levels of fatigue (during the previous 24 hours). Items four to nine examine the extent to which fatigue interferes with everyday life, such as mood, relationships and enjoyment. This scale has been used in samples of cancer survivors and has been shown to have good validity and reliability (Cronbach’s α 0.95 to 0.96 [40].

For economic evaluation, items assessing health service use, caring responsibilities and improvements from a patient perspective will also be included. The objective of the economic analysis is to identify the costs (and cost savings) associated with RESTORE compared with the leaflet comparator. The analysis will take the perspective of the health and social care sectors, including third-sector organizations (for example, hospice care). Patients’ use of these resources will be collected by way of a bespoke patient questionnaire. The resources associated with provision and implementation of RESTORE will be included in the analysis. These will be based on routine data, such as administrative records, as well as a detailed description of the implementation and the development process of the intervention. Unit costs for health service resources will be obtained from national sources such as the Personal Social Services Research Unit (PSSRU), the British National Formulary and NHS Reference cost database. Where national unit costs are not available, the finance departments of trusts participating in the study will be asked to provide local cost data. The mean of these costs will be used as the unit cost estimate in the analysis. The results will be presented alongside the primary and secondary outcomes as a cost consequence analysis.

All primary and secondary outcome measures will be assessed at baseline (T0), six weeks (T1; completion of intervention) and three months (T2; end of study). T2 will act as our primary endpoint.

This is an exploratory trial and therefore a mixed-methods process evaluation will evaluate the feasibility and acceptability of the intervention. Quantitatively, adherence to the intervention (that is, number of sessions completed) will be examined, as will completion rates of questionnaire items at all three time points. Recruitment rates will be calculated based on the number of eligible patients approached versus those who consent to take part in the trial. The proportion of ineligible patients will also be described and reasons for ineligibility documented. Eligible patients who decline participation will also be asked to volunteer a reason for this. Acceptability of the intervention will be inferred by attrition rates. Additionally, semistructured telephone interviews with participants will explore feasibility and acceptability in more depth. We will recruit a maximum variation sample of men (*n* ≈ 15) and women (*n* ≈ 15) where variation will be by (a) cancer type and time since treatment completion, and (b) compliance with the intervention. The interview schedule will be structured to identify, describe and explain the impact of CRF on participants, the perceived acceptability of online interventions and the value of RESTORE to them (for example, improved confidence, reduced interference of CRF in daily life), and factors that promote or inhibit the integration of RESTORE into everyday life. Telephone interviews will be transcribed and analyzed using directed content analysis [41]. Analysis will be informed by Normalization Process Theory [42,43].

### Sample size

We aim to recruit 125 patients to this trial. Currently, there is no definitive guidance on the size of exploratory trials. We feel that this is an achievable sample size based on the resources available and is adequate to allow for a relatively high attrition rate while still leaving a reasonable final sample. Also, the primary outcome measure (PSEFSM) could not be used to determine a power calculation as the measure is new and insufficient data are available. A definitive sample size for a large scale RCT will be determined from results of this trial.

### Analysis

The principal analysis will involve fitting between group, repeated measures models with two levels of treatment variable (intervention group, leaflet group) and three time points (T0, T1, T2) to the primary and secondary outcome measures. Distribution of the outcomes will be inspected to identify the appropriate form of the response variables for the modelling. Model assumptions will be checked and outcomes will be transformed where there is strong evidence of non-normality, for example by taking logs, dichotomizing or categorizing into three or more ordered categories. The appropriate mixed effects, repeated measures model (normal, binary or ordinal) will be fitted with random coefficients on the time points and a random intercept for trust to control for within-subject and within-Trust correlations. All data will be analyzed blind to treatment condition and intention to treat analysis will be undertaken. Auxiliary analyses will assess the interaction of potential modifiers (for example, age, sex, socio-economic status, cancer treatment received, cancer type) with treatment in the models. Change over time of the primary and all secondary outcome measures will be examined.

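### The principal model takes pre-randomisation T0 as a response without baseline adjustment and does not say which term gives the T2 effect; equal T0 arm means would add precision at no cost

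*Protocol article*

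**What the plan says.** All references are to the protocol article.

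- **Outcome and time.** The abstract says "The primary outcome is a change in Perceived Self-Efficacy for Fatigue Self-Management". The Assessments section adds "T2 will act as our primary endpoint", that is, three months.
- **Timing of T0.** The same section states: "Baseline assessment (T0) will be completed online immediately after participants consent to the study and prior to randomization".
- **Principal model.** The Analysis section describes "fitting between group, repeated measures models with two levels of treatment variable (intervention group, leaflet group) and three time points (T0, T1, T2", with "random coefficients on the time points and a random intercept for trust to control for within-subject and within-Trust correlations".
- **Other analyses.** "Auxiliary analyses will assess the interaction of potential modifiers" with treatment; and "Change over time of the primary and all secondary outcome measures will be examined".

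The Analysis section specifies the treatment factor, the visits, the random effects and the response families. It mentions no baseline covariate, no common T0 mean, no treatment-by-visit term and no contrast at T2.

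**The concern.** Because T0 is measured before allocation, the two arms have the same expected value at T0. A model that estimates a separate T0 mean for each arm does not use that fact. It subtracts the chance baseline difference in full, when only the part that predicts T2 needs to be removed. The cost is precision.

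The second issue is that one fitted model offers several treatment terms: an effect pooled over the visits, a joint treatment-by-visit test, and a single contrast at T2. They answer different questions, and the article does not say which is the primary result.

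Two things are at stake. The Sample size section allows for fairly high attrition, so precision should not be given away. It also says that the sample size of the definitive trial will come from these results, so the effect carried forward should be the T2 effect.

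**Working it through.** **Inputs from the article:** "We aim to recruit 125 patients to this trial"; allocation 1:1; visits T0, T1 and T2; T0 before randomisation; T2 primary. The article gives no power, SD, effect size, visit correlation or attrition figure, so there is no stated figure to reproduce.

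**Assumptions:** a normal outcome with SD 1 at each visit; correlation r between any two visits, from 0.3 to 0.8; effect d = 0.5 SD; two-sided 5% test; 30% attrition, so 125 × 0.7 / 2 = 43.75, about 44 per arm. Trust effects are ignored.

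**Per-patient variance of each estimate**

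- T2 minus T0, arm-specific T0 means: 2(1 − r); expected value d.
- T2 with T0 as covariate, or with equal T0 means: 1 − r²; expected value d.
- Treatment term pooled over three visits: (1 + 2r)/3; expected value (0 + d + d)/3 = 2d/3 if the effect is equal at T1 and T2, or (0 + 0 + d)/3 = d/3 if it is present only at T2.

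The variance ratio of the first to the second is 2(1 − r)/[(1 − r)(1 + r)] = 2/(1 + r). SE = √(2 × variance / n per arm); power = Φ(effect/SE − 1.96).

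**At r = 0.5, 44 per arm**

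- T2 minus T0: SE = √(2 × 1.00/44) = 0.213; z = 0.5/0.213 = 2.35; power 65%.
- Baseline-adjusted: SE = √(2 × 0.75/44) = 0.185; z = 2.71; power 77%.
- Pooled term, equal effects at T1 and T2: SE = √(2 × 0.667/44) = 0.174; estimate 0.33; z = 1.92; power 48%.
- Pooled term, effect only at T2: estimate 0.17; power 16%.

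**Over the range of r**

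| r | Variance ratio | Power, T2 minus T0 | Power, adjusted |
|---|---|---|---|
| 0.3 | 2/1.3 = 1.54 | 51% | 69% |
| 0.5 | 2/1.5 = 1.33 | 65% | 77% |
| 0.7 | 2/1.7 = 1.18 | 86% | 91% |
| 0.8 | 2/1.8 = 1.11 | 96% | 97% |

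With all 125 analysed, the powers at r = 0.3, 0.5 and 0.7 are 66%, 80% and 95% for T2 minus T0, and 83%, 90% and 97.5% adjusted.

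**Simulation check.** 400 simulated trials of 125 were analysed by generalised least squares with known covariance. T0 and T1 were complete and 30% of T2 values were missing. At r = 0.5 the SE was 0.203 with arm-specific T0 means and 0.182 with a common mean (power 66% and 75%). At r = 0.7 it was 0.158 and 0.149. All mean estimates were close to 0.5. The variance ratios, (0.203/0.182)² = 1.24 and (0.158/0.149)² = 1.12, are somewhat below 1.33 and 1.18, because both models carry the same added variance from the missing T2 values.

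**Does the direction depend on equal SDs?** With SDs s0 and s2 at T0 and T2, the change-score variance less the adjusted variance is (s0² + s2² − 2r·s0·s2) − s2²(1 − r²) = (s0 − r·s2)². This is never negative, so adjustment does not lose precision in large samples whatever the two SDs are.

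**The case against.** A journal article condenses the full protocol. Which term is reported, and how the T0 means are set up, may be given in a full protocol or analysis plan that is not shown. The trial is exploratory and claims no power. Every figure above rests on assumed values, and random coefficients over time need not give equal correlations.

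Much of this stands. The unnamed contrast is, on its own, only a point to clarify. The equal-correlation assumption matters less than it seems: the 2/(1 + r) ratio uses only the T0-T2 correlation and equal SDs at those two visits, and the direction of the result needs neither.

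A reader might infer three stronger things that the documents do not support:

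- **That having T0 among the responses is itself an error.** It is not. With a common T0 mean it costs nothing, and the article does not rule that out.
- **That the analysis misses its primary endpoint.** The outcome is a change, the endpoint is T2, and the model can give the between-arm difference in change to T2. Because T0 precedes randomisation, that contrast has the same expectation as the difference at T2.
- **That the effect will be diluted to 0.33 SD.** This follows only if the pooled treatment term is the reported result. The article does not say so, and that term would fit neither the change outcome nor the T2 endpoint.

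What remains is a choice of method. The article gives the model in some detail and includes no baseline adjustment, although T0 is collected before anyone is randomised.

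**Conclusion.** The point holds as a worthwhile improvement to the method, not as an error that invalidates the analysis. In its ordinary form, with arm-specific T0 means, the model gives an unbiased T2 contrast whose variance, with complete data, is 11% to 54% above that of a baseline-adjusted one for r from 0.8 down to 0.3. The loss is small if PSEFSM scores are strongly correlated over three months and substantial if they are not; the documents do not say which. The power figures illustrate this under the assumed effect and attrition, and no power stated in the plan is missed. Dilution to two thirds or one third of the effect is conditional on reporting the pooled term, which naming the contrast would rule out.

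**What to change.** Add one paragraph to the Analysis section or the analysis plan:

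- The principal result is the between-arm difference in PSEFSM at T2; the difference at T1 is secondary.
- It is estimated from the same mixed model over T0, T1 and T2, with the arm means at T0 constrained equal and arm-by-visit terms only at T1 and T2. Alternatively, T0 is a covariate and T1 and T2 are the responses.
- The secondary outcomes use the same model.
- The modifier interactions are tested on the T2 contrast, not on a treatment term averaged over the visits.

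With the constrained form, every randomised participant with a baseline score stays in the intention-to-treat analysis. The change uses data already being collected and needs no extra patients.
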